#### Implementation outcomes

The implementation outcomes assessed are guided by the Consolidated Framework for Implementation Research (CFIR) and include intervention adoption, acceptability, appropriateness, feasibility, fidelity, and sustainment evaluations [28, 50].

### Recruitment and informed consent

TH in the study area were identified through a door-to-door census of the study region conducted by the study team in June 2023. All TH meeting the eligibility criteria had their GPS location documented. Forty-four TH were randomly selected from this census for possible trial participation and invited to participate as cluster sites. All TH provided written informed consent.

The participating TH will identify eligible PLWH. For this study, TH will not recruit PLWH outside of their practice. TH will provide basic information about the study to potentially eligible participants, and if the participant is interested, the TH will ask them for permission to be contacted by the study team. Members of the study team will contact the eligible PLWH by mobile phone within 24 business hours to provide additional information about the study and confirm interest in participating. RAs will arrange for an in-person meeting at a convenient location to request written informed consent from the potential participant and collect a venous blood sample for HIV viral load testing. If the participant wishes to participate, the study staff member will have the participant sign and date the consent form in the space provided. If the PLWH has limited literacy, they will select someone to witness the entire consent process. If the participant is unable to sign or print their name or date, the witness will print the participant’s name and date, and the participant will use the ink pad to make their thumbprint. The witness will sign and date the consent form in the space provided. All questions from the study surveys and questionnaires will be delivered verbally to accommodate those with limited literacy.

For implementation evaluations, clinicians and policymakers will be recruited through purposive sampling through the study referral HIV clinics and local and Ministry of Health offices, respectively. They will provide written informed consent for participation.

Informed consent forms will be written in nontechnical language, translated from English into Runyankole (local language) and then translated back to English to ensure accuracy. The consent process will be conducted by trained study team members who are fluent in Runyankole and English. Study team members will all be required to maintain Good Clinical Practice certification and will be trained on the research protocol. Recruitment is targeted for completion by the end of July 2025. All study participants are volunteers and can leave the study at any time without recourse. This is clearly stated during the informed consent process.

### Sample size

Study power calculations are based on the primary hypothesis that the intervention will improve viral suppression by 20% using standardized methods for cluster randomized trials [51]. Based on population-level data from the Ugandan Ministry of Health, we assume that the proportion of PLWH achieving the primary outcome of viral suppression will be 60% in the control arm versus 80% in the intervention arm [3]. The results of prior community-based and psychosocial HIV support interventions were used to inform this estimated effect size [32, 52, 53]. To ensure 85% power to detect a difference of ≥ 20% in viral suppression between arms and assuming a 10% loss-to-follow-up rate, we will enroll a minimum of 16 PLWH in each cluster. The target sample size is 650 PLWH, with 325 PLWH in each arm. Forty-four TH will be enrolled as cluster sites, with 22 in each study arm.

As part of the implementation evaluation, we will purposively recruit 20 PLWH, 20 HIV clinicians, and 7 policymakers for participation. The sample size of 20 HIV clinicians is based on prior research showing that thematic and conceptual data saturation is obtained after 12–16 interviews have been conducted within a subgroup [54, 55]. Due to the limited number of policymakers, 7 interviews will be conducted to understand local and national government priorities and implementation context.

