**Methods:**

This cluster randomized hybrid type 1 effectiveness-implementation trial will be conducted among 44 traditional healers in two districts of southwestern Uganda. Healers were randomized 1:1 into study arms, where healers in the intervention arm will provide 12 months of psychosocial support to adults with unsuppressed HIV viral loads receiving care at their practices. A total of 650 adults with unsuppressed HIV viral loads will be recruited from healer clusters in the Mbarara and Rwampara districts. The primary study outcome is HIV viral load measured at 12 months after enrollment, which will be analyzed by intention-to-treat. Secondary clinical outcome measures include (re)initiation of HIV care, antiretroviral therapy adherence, and retention in care. The implementation outcomes of adoption, fidelity, appropriateness, and acceptability will be evaluated through key informant interviews and structured surveys at baseline, 3, 9, 12, and 24 months. Sustainability will be measured through HIV viral load measurements at 24 months following enrollment.

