## Background

In Uganda—as in most African countries—the majority of the population resides in rural communities [1]. Rural areas bear a disproportionate burden of HIV; in Uganda, there is a nearly threefold increase in the prevalence of HIV in some rural areas compared to the national level [2]. According to the most recent Ugandan population-based HIV impact assessment, only 66% of rural people living with HIV (PLWH) are aware of their status, compared to 86% of urban PLWH. Furthermore, only 39% of rural PLWH are on antiretroviral therapy (ART), and 23% are virally suppressed, compared to 75% and 59% of urban PLWH, respectively [3]. Overall, rural populations demonstrate 15–25% lower engagement in the HIV continuum than their urban counterparts [4]. These data indicate a pressing need for appropriate and effective strategies to improve rural HIV care to achieve the UNAIDS 95–95-95 benchmarks [5].

In rural areas, PLWH encounter many challenges accessing and consistently engaging in HIV care. Clinics are few and far between, often necessitating expensive motorized transportation. Consequently, regular clinic visits are challenging for individuals living in poverty [6–8]. Moreover, a considerable number of rural PLWH harbor mistrust toward medical care, stemming from fears of stigma associated with being spotted at an HIV clinic, concerns over breaches in confidentiality, and perceived mistreatment from clinicians [9–12]. A lack of social support and diminished self-efficacy among these populations further contribute to disinterest and disengagement from HIV care [13, 14]. Therefore, community-based strategies designed to overcome these obstacles will likely be particularly beneficial for rural PLWH.

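### The sample-size paragraph asks for at least 16 participants in each of 44 clusters (704) but sets the target at 650; the source of its 60% control rate also needs stating

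*Protocol article*

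**What the plan says.** The Sample size section gives three enrolment figures in consecutive sentences:

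- per cluster, after stating 85% power and 10% loss to follow-up: "we will enroll a minimum of 16 PLWH in each cluster";
- in total: "The target sample size is 650 PLWH, with 325 PLWH in each arm";
- clusters: "Forty-four TH will be enrolled as cluster sites, with 22 in each study arm".

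The abstract treats the total as a recruitment figure: "A total of 650 adults with unsuppressed HIV viral loads will be recruited from healer clusters". The Quantitative data collection section also uses 650, and the Oversight and monitoring section presents interim results after the 325th enrolment, which is half of 650.

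On the control rate, the same section cites population-level Ministry of Health data (reference 3): "we assume that the proportion of PLWH achieving the primary outcome of viral suppression will be 60% in the control arm", against 80% with the intervention. The Background reports from reference 3 that "only 39% of rural PLWH are on antiretroviral therapy (ART), and 23% are virally suppressed, compared to 75% and 59% of urban PLWH". The Study setting section places the trial in rural districts. The inclusion criteria require a viral load of at least 200 copies/mL at enrolment and, for those already diagnosed, being out of care by self-report.

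**The concern.** A minimum per cluster, a number of clusters and a total are tied together by multiplication, and here they do not multiply out. Field staff have two incompatible instructions: stop at 650, or continue until every healer has 16. With 650 participants, some clusters must fall below the minimum, so the plan would be breached however well recruitment went. The 325th-participant interim trigger fits one total and not the other.

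The secondary matter is the provenance of the 60%. A reader who follows reference 3 back to the Background finds a rural figure of 23% and an urban figure of 59%. The assumed rate lies next to the urban one, although the trial is rural and everyone starts unsuppressed. The article makes checking the sample-size assumptions the first aim of its interim analysis, so the basis of the reference rate should be clear beforehand.

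**Working it through.** **Inputs from the article:** at least 16 enrolled per cluster; 44 clusters, 22 per arm; target 650, 325 per arm; 60% against 80%; 85% power; 10% loss; p < 0.05. **Assumed here:** a two-sided test, and a range for the clustering parameter, which the article does not give.

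**1. The three enrolment figures**

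- 44 × 16 = 704; 22 × 16 = 352 per arm.
- 704 − 650 = 54; 54/650 = 8.3%.
- 650/44 = 14.8 per cluster, below 16.
- 650/16 = 40.6 clusters, not 44.

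**2. Does attrition reconcile them?**

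- If 650 were the number left after losses from 704: 704 × 0.9 = 634. That is near 650 but not equal to it, and the abstract says 650 are recruited.
- If 650 were the number needed after losses: 650/0.9 = 722 enrolled, which is neither figure.

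**3. Can the stated design be reproduced?**

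Without clustering, n per arm = [1.96 √(2 × 0.7 × 0.3) + 1.036 √(0.24 + 0.16)]² / 0.2² = 93, or 104 after 10% loss. The total of 650 therefore depends on a clustering allowance.

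The Hayes–Bennett formula for clusters per arm, with m analysed per cluster and between-cluster coefficient of variation k, is

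c = 1 + (1.96 + 1.036)² × [(0.24 + 0.16)/m + k²(0.36 + 0.64)] / 0.04.

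Taking k = 0.25:

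| Enrolled | m after 10% loss | c | Power with c = 22 |
|---|---|---|---|
| 704 | 16 × 0.9 = 14.4 | 21.3 | 86.2% |
| 650 | 14.8 × 0.9 = 13.3 | 21.8 | 85.4% |

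Power is Φ(√[21 × 0.04 / (0.4/m + 0.0625)] − 1.96). Both totals round up to 22 clusters per arm, so 22 is consistent with either.

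**4. Cross-check with an intracluster correlation (ICC)**

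The effective n per arm is (N/2)/[1 + (N/44 − 1) × ICC]. Power for 60% against 80%:

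| ICC | N = 650 | N = 704 |
|---|---|---|
| 0.05 | 99.1% | 99.3% |
| 0.10 | 95.4% | 95.9% |
| 0.15 | 89.4% | 90.0% |
| 0.20 | 82.5% | 83.1% |

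The two totals differ by less than 1 point throughout. If the lost tenth is instead carried as unsuppressed (60% × 0.9 = 54% against 80% × 0.9 = 72%), they differ by 0.7 to 1.0 points over the same range.

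**5. The control rate**

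From the Background figures, suppression among those on treatment is 23/39 = 59% (rural) and 59/75 = 79% (urban). So 60% lies close to two different numbers: suppression among all urban people with HIV, and suppression among rural people on treatment.

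Power at N = 650 with the 20-point difference held:

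| ICC | 60% v 80% | 40% v 60% | 23% v 43% |
|---|---|---|---|
| 0.05 | 99.1% | 97.7% | 98.8% |
| 0.10 | 95.4% | 91.5% | 94.4% |
| 0.15 | 89.4% | 83.4% | 87.8% |
| 0.20 | 82.5% | 75.3% | 80.5% |

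At 23% the cost is 2 points or less. It is larger, up to about 7 points, for a mid-range rate such as 40%, where the binomial variance is greatest. If k rather than the ICC is held fixed (0.252, calibrated to 85% at 60% v 80%), power rises: 94% at 40% and 99% at 23%.

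**The case against.** The best defence is that the mismatch is a matter of wording. Either total supports about 85% power with 22 clusters per arm, and an analyst would not notice the difference. That stands as far as power goes, and a reader who inferred that the power statement fits neither total would be wrong. It does not rescue the paragraph as an enrolment instruction. The word minimum rules out reading 16 as an average, and the loss allowance is already inside it.

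On the control rate, it is tempting to conclude that the trial used an urban rate by mistake, that 23% is correct, and that the trial is underpowered. The documents do not support this. The rural on-treatment figure of 59% is an equally close origin for 60%, and reference 3 may hold other figures. The 23% covers all rural people with HIV, of whom the Background says only 66% know their status. Trial participants in both arms are identified, referred to free care and given transport funds for the first visit. Equally, 59% among those on treatment is not plainly right, since not everyone referred will start and stay in care.

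Much lower power appears only if the ratio 80/60 = 1.33 is carried to a lower base; 23% against 30.7%, for example, gives 40% to 21% over ICC 0.05 to 0.20. The article does not assume a relative effect: the pair 60% and 80% shows that its 20% is an absolute difference.

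A reader might also infer from the entry criterion of five adult clients a month that 16 per healer is out of reach. That criterion is a floor, and the article gives no actual volumes from which to judge.

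**Conclusion.** The contradiction is certain and needs no assumption: 16 per cluster, 44 clusters and 650 participants cannot all be true. It amounts to 54 participants, or 8.3% of the target. Its effect on power is about 1 point or less, given a two-sided 5% test and the clustering values shown. It is a wrong recruitment figure, not a defect in the trial's ability to answer its question.

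The control-rate point is secondary and limited. The article credits 60% to a source for which it reports 23% and 59%, and does not say which figure was used or why it fits rural adults who are all unsuppressed at entry. What is lacking is the explanation; the rate is not shown to be wrong. With the 20-point difference held, moving to 23% changes power little.

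**What to change.** In the Sample size section, replace the minimum of 16 per cluster with *an average of about 15 PLWH per cluster (650/44)*. Keep 650 and the interim trigger at the 325th participant, and confirm the 85% power at that cluster size. This costs one sentence, a rerun of the existing calculation and no extra participants. If 16 in every cluster is really intended, the target has to become 704 (352 per arm), which means 54 more participants and a different halfway point.

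In the same section, add a sentence naming the figure behind the 60% control rate (for example, suppression among rural people on treatment, 23/39 = 59%) and why it applies to this population, or restate the assumption. This also costs only wording, unless the sponsor changes the rate, in which case the power calculation should be repeated.

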### Randomization

Among the TH in the region who met the study inclusion criteria, 44 were randomly selected to participate in the study. Eligible TH were assigned to a stratum corresponding with geographic distances either near (≤ 5 km) or far (> 5 km) from the study referral HIV clinics (Fig. 2). Five kilometers will be used to define strata as the median distance from TH in the study region to the nearest HIV clinic. Within each stratum, subgroups of TH were created to include one TH and any others located ≤ 3 km away from one another to minimize contamination between clusters.

Using computer-generated random assignment, the principal investigator randomly selected 44 TH from the subgroups. Using another computer-generated random assignment, each of the 44 selected TH was randomized at a 1:1 ratio within each stratum and assigned to either the intervention or control arm. Following randomization, TH were informed of their assigned study arm by a member of the study team and informed of the upcoming training requirements.

### Blinding

There will be no blinding in this study except during the data analysis. Due to the evident morphological differences between the intervention (psychosocial support) and control (no psychosocial support) groups, both participants and study team members will be aware of study arm allocations following randomization. The study statistician will be blinded to study arm allocations during analysis.

### Participant timeline

Please see Table 3 for the detailed schedules of activities for each participant group.

**Table 3 Tab3:** Detailed schedules of activities for each participant group

People Living with HIV (PLWH) Schedule of Activities							
**Period/Phase**	**Screening/Baseline**	**Day 15**	**Day 29**^**d**^	**Day 43**^**d**^	**Day 57**^**d**^	**12-Month F/u**	**24-Month F/u**
**Study Day**	**D1**	**D15**	**D29**	**D43**	**D57**	**D365**	**D731**
**Study Week**	**W1**	**W2**	**W4**	**W6**	**W8**	**W52**	**W104**
**Study Visit**	**1**	**2**	**3**	**4**	**5**	**6**	**7**
**Window (Days)**		** ± 7**	** ± 7**	** ± 7**	** ± 7**	** + 30**	** + 30**
Oraquick HIV Testing^a^	x						
Case Adherence Index Questionnaire^b^	x						
Informed Consent	x						
Assessment of Inclusion/Exclusion Criteria	x						
Demographic Collection^c^	x						
Medical History	x						
HIV History	x						
FSSQ [56]	x					x	x
HIV-ASES [57]	x					x	x
HIV Stigma Questionnaire [58]	x					x	x
HIV-SMS [59]	x					x	x
HIV-KQ-18 [60]	x					x	x
Quality of Life (MOS-HIV) [61]	x					x	x
TFA [62]	x					x	x
Dried Blood Sampling						x	x
Hair Sample Collection						x	
Patient Enrollment card	x					x	x
**Interviews (will be conducted for specified patients)**	x					x	x
*Perceived complexity and relative advantage of the intervention*	x					x	
*Perceived successful strategies with implementers & patients*	x					x	
*Perceived roles of intervention champions & opinion leaders*	x					x	
*Facilitators & barriers to implementation*						x	
*Sustained impact of intervention on HIV continuum of care*							x
*Integration into routine practice; reasons for maintenance/discontinuation*							x
Phone Call to Patient about Linkage to HIV Care		x	x	x	x		

^a^Oraquick HIV Testing to be administered prior to study enrollment to adults reporting no prior HIV diagnosis or HIV testing within the prior 12 months

^b^Case Adherence Index Questionnaire to be administered prior to study enrollment and to suspected defaulting participants only

^c^Demographics include includes age, sex, education, religious affiliation, household size, marital status, highest level of education

^d^Visit only occurs if PLWH has not linked to care within 7 days

All PLWH and TH will meet for scheduled study visits with a member of the study team at enrollment (baseline) and then at 12 and 24 months following enrollment to complete structured surveys. Qualitative interviews will be held throughout the study period, beginning at the time of enrollment. We will invite all intervention arms TH and clinical liaisons, as well as a sample of PLWH, HIV clinicians, and policymakers, to participate in these interviews. Study participants may request to discontinue participation in the study at any time. If a study participant fails to attend their 12-month or 24-month research study visits, they will be considered lost to follow-up. All participant data will be analyzed under the principle of intention-to-treat.

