#### Effectiveness outcomes

The primary study outcome is HIV viral suppression (serum viral load < 200 copies/mL) among PLWH at 12 months following study enrollment. Plasma samples will be processed to obtain HIV-1 RNA viral load concentrations at the Epicenter Mbarara Research Base using the Abbott HIV-1 assay. This test is > 90% sensitive and specific [45–47]. The secondary outcomes will be (1) (re)linkage to care within 7 days; (2) ART (re)initiation; (3) ART adherence at 12 months after linkage to care, defined as a binary outcome of hair tenofovir concentration (> 0.023 ng/mg, reflecting four or more ART doses per week); and (4) retention in HIV clinic care after 12 months [48, 49].

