#### Retention of PLWH participants

Upon enrollment, study participants will be assigned a unique identification number and will complete a detailed locator information form that includes contact information for the participant, multiple participant-designated contact persons, and detailed residence and workplace information. These designated contact persons will be peers or family members whom the study team can contact if the participant is not reachable for follow-up through other means. Study staff will contact participating PLWH via mobile phone following enrollment to assess for (re)linkage to care within 7 days of study enrollment. For participants who cannot be reached by phone during the initial follow-up, study staff will call a backup contact to inquire about the participant’s whereabouts (taking care not to mention HIV status or the purpose of the study). If participants are not reachable via their designated contacts, study staff will invoke the assistance of participants’ TH to help locate the individual, as TH are often in regular contact with their clients. Participants will be notified 2 weeks by phone call prior to the study staff’s 12- and 24-month visits and receive a reminder the day before via text message.

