#### Statistical methods for primary outcomes

The primary outcome of the trial is viral suppression, defined as a plasma HIV-1 RNA concentration < 200 copies/mL [38]. An intent-to-treat analysis will be used to assess the primary outcome at 12 months among PLWH in the intervention group compared with the control group. A mixed effects logistic regression model—with individual PLWH in level 1 nested within TH in level 2—will be applied to determine if the intervention increases the relative risk of viral load suppression compared with the control. We will conduct additional analyses to account for the heterogeneous effect of individual PLWH-level parameters on viral suppression in the mixed effects logistic regression model. The individual PLWH-level parameters to be accounted for may include newly diagnosed patients with HIV at enrollment vs. previously diagnosed patients; demographic variables such as age, sex, and socioeconomic status; and survey measures such as social support and HIV stigma. We will also apply an estimand framework analysis to consider the impact of intercurrent events on the primary outcome of HIV viral suppression. *p* < 0.05 will considered to indicate statistical significance in this primary analysis. Participants lost to follow-up will be considered virally unsuppressed for the primary outcome analysis.

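### As written, missing the 24-month visit turns a measured 12-month viral suppression into a primary-outcome failure; the sample size section should also say how its 60% and 80% treat losses

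*Protocol article*

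**What the plan says.** All references are to the protocol article.

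- **Participant timeline** defines loss: "If a study participant fails to attend their 12-month or 24-month research study visits, they will be considered lost to follow-up". No other section defines it or narrows it to one visit.
- **Statistical methods for primary outcomes** applies it: "Participants lost to follow-up will be considered virally unsuppressed for the primary outcome analysis".
- **Effectiveness outcomes** fixes the time point: "The primary study outcome is HIV viral suppression (serum viral load < 200 copies/mL) among PLWH at 12 months following study enrollment". Table 2 gives the same time point and lists the 24-month viral load separately, as sustainment.
- **Interim analyses** places an interim look after half of the participants have completed their 12-month evaluations.
- **Sample size** assumes that "viral suppression will be 60% in the control arm versus 80% in the intervention arm", and continues: "To ensure 85% power to detect a difference of ≥ 20% in viral suppression between arms and assuming a 10% loss-to-follow-up rate", followed by "we will enroll a minimum of 16 PLWH in each cluster". The target is 650 participants from 44 healers. No ICC or between-cluster coefficient of variation is stated.
- **Interventions** gives participants in the intervention arm weekly and then monthly healer meetings; control sites add no such support. **Retention of PLWH participants** calls on healers in both arms to help find people who cannot be reached, "as TH are often in regular contact with their clients".

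**The concern.** The definition and the scoring rule are both explicit, and together they let an event at month 24 overwrite a result observed at month 12. A programmer following the text would discard valid primary data, and the 12-month result could not be closed until the last 24-month visit.

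Two further matters follow from scoring missing as unsuppressed. First, the sample size section ties the 10% loss allowance to the enrolment number, as if those people left the analysis, whereas the analysis keeps them in as failures. Whether the assumed 60% and 80% already reflect that is not stated. Second, healer contact differs by arm by design, so if it changes who attends at month 12, the rule counts the difference in attendance as a difference in suppression.

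**Working it through.** **1. The rule applied to one participant.** Month 12: attended, viral load below 200 copies/mL, so suppressed. Month 24: not attended, so lost to follow-up under Participant timeline. Lost to follow-up, so unsuppressed in the primary analysis under Statistical methods. The measured value has been replaced.

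**2. When the outcome becomes final.** Recruitment is due to end about 30 July 2025 (Trial status). Table 3 puts the two visits at day 365 and day 731, each with a window of +30 days. The last 12-month visit therefore falls by about the end of August 2026 and the last 24-month visit by about the end of August 2027. Under the literal rule the primary result stays open for that extra year. The interim analysis, triggered by completed 12-month evaluations, would use outcomes that could still change.

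**3. Size of the recoding.** If a fraction f of those measured as suppressed misses month 24, the arm's rate is multiplied by (1 − f). The documents give no f. Purely as assumptions, and before any month-12 loss: f = 5% turns 60% and 80% into 57% and 76%; f = 10% turns them into 54% and 72%.

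**4. The stated 85% power.** Inputs from Sample size: 22 clusters per arm, 650/44 = 14.77 per cluster, 14.77 × 0.9 = 13.30 followed, 60% against 80%. Alpha is 0.05, assumed two-sided. Formulas, with ρ the ICC:

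- effective n per arm = 22m / [1 + (m − 1)ρ]
- power = Φ{[Δ√n − 1.96√(2p̄(1 − p̄))] / √(p₀(1 − p₀) + p₁(1 − p₁))}

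Without clustering, 93 per arm gives 85% power, and the 292.5 followed per arm would give more than 99.9%. The 85% therefore needs a design effect of about 292.5/93 = 3.15, that is ρ = 2.15/12.30 = 0.175 (about 0.18 with 16 per cluster or an unpooled variance). This ρ is solved for, not stated, so the plan's figure is not reproduced.

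**5. The same power with losses scored as failures.** If 60% and 80% are rates among those followed, then 0.9 × 60% = 54% and 0.9 × 80% = 72%, a difference of 18 points, with all 650 analysed (m = 14.77). At ρ = 0.175 the design effect is 1 + 13.77 × 0.175 = 3.41, effective n = 325/3.41 = 95.3 per arm, and power is 73%. If instead the between-cluster variance shrinks with the rates (× 0.9² = 0.81), power is 82%. The coefficient-of-variation formula, with k = 0.252 solved to give 85%, also gives 82%.

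| Assumed ICC | 60% v 80%, 10% excluded | 54% v 72%, ICC held | 54% v 72%, variance × 0.81 |
|---|---|---|---|
| 0.05 | 98.8% | 95.8% | 97.7% |
| 0.10 | 94.7% | 87.3% | 92.9% |
| 0.15 | 88.5% | 77.9% | 86.6% |
| about 0.18 (solved) | 85% | 73% | 82% |

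The last column uses an unpooled variance. With the ICC held, power stays at or above 85% up to an ICC of about 0.11. If 60% and 80% already count losses as failures, nothing is diluted and power at ρ = 0.175 is about 86%.

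**6. Unequal follow-up, illustration only.** With 60% true suppression in both arms and 90% against 80% followed, the rule shows 0.6 × 0.9 = 54% against 0.6 × 0.8 = 48%, an apparent benefit of 6 points. With 92% against 88% it shows 55.2% against 52.8%, or 2.4 points. Neither gap comes from the documents.

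**The case against.** The best defence is that the definition can be read visit by visit: missing month 12 means lost for the 12-month outcome, and missing month 24 means lost for the 24-month one. The surrounding text favours that intent. The primary outcome is tied to 12 months throughout, month 24 has its own sustainment outcome, and an interim look at completed 12-month evaluations makes sense only if those outcomes are settled. A reader might infer that the sponsor plans to overwrite 12-month results; the documents do not support that as an intention. What stands is that no sentence limits the rule, so the text as written produces the overwriting.

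A reader might also infer that 85% power is wrong, or that the true power is some particular lower figure. That does not follow. With no ICC stated, any shortfall rests on treating 85% as exact, on 60% and 80% being rates among those followed, and on a choice of variance model. The section draws its rates from population-level data and does not say that they exclude people lost to study follow-up.

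Nor do the documents show biased retention. Locator forms, designated contacts, reminders and healer tracing serve both arms, control healers are also paid and given phone vouchers, and healer tracing is described for people unreachable at the initial follow-up. Unequal contact is built into the design; its effect on attendance is unknown.

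Finally, scoring missing as unsuppressed is an explicit and permissible choice, and the plan adds an estimand analysis of intercurrent events. Details of multiple imputation belong in a statistical analysis plan that is not shown here, so their absence is not an error.

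**Conclusion.** The either-visit definition is wrong as written and needs correcting before outcomes are analysed. That conclusion rests on the text alone and needs no numerical assumption. How many participants it would affect cannot be derived from the documents.

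The power point is secondary and conditional: Sample size does not show whether it reflects the scoring rule. If 60% and 80% are rates among those followed and 85% was exact, power for the planned analysis would be about 73% to 82%, depending on the variance model. At an ICC of 0.10 or below it stays above 85%.

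The follow-up point is a mechanism that deserves transparent reporting, not a demonstrated bias.

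**What to change.** 1. **Participant timeline and Statistical methods for primary outcomes.** State that, for the primary outcome, a participant is lost to follow-up only if no plasma viral load is available in the 12-month window, and that a missed 24-month visit affects the sustainment outcome alone. Missing scored as unsuppressed can stay.
2. **Sample size.** Say whether the assumed 60% and 80% already count losses as failures, and give the ICC that was used. If they are rates among those followed, restate power for 54% against 72% with all 650 analysed, using that ICC rather than one solved backwards.
3. **Reporting.** Show 12-month retention by arm beside the primary result.

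The cost is a sentence or two in each of three sections, one recalculation and one extra line in the results. No data collection changes. The restated power may prove somewhat lower than 85%, or may not, depending on the ICC.
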